### Interventions

The patient will be allocated to one of the following treatments:o*Flaminal® Forte:* treatment with Flaminal® Forte (glucose oxidase-lactoperoxidase guaiacol complex of 50 g in 5.5 % alginogel) will be initiated within 24 hours after admission. Before applying Flaminal® Forte on the wound, pain medication must be given. Paracetamol, Oxynorm and Oxycontin will be used as standard pain medication. The usage and doses of pain medication will be monitored. The burn wound will be cleaned and rinsed with Prontosan® followed by careful dabbing and drying of the wound. The wound will then be covered with a non-adhesive dressing on which a sufficiently thick layer (4–5 mm) of Flaminal® Forte has been applied. A net bandage/dressing will be used to keep the dressing in place. Dressing changes will be performed daily during the first 3 days post burn and thereafter every other day. If an infection is suspected, or in case of leaking or insufficient gel, the dressing with Flaminal® Forte may be changed daily after 3 days post burn. In case of wound colonization or infection, treatment with Flaminal® Forte will be changed to another relevant treatment based on the results of the wound cultureo*Flamazine®:* treatment with Flamazine® (silver sulfadiazine 10 mg/g in hydrophilic crème base) will consist of daily washing and application of Flamazine®. Before applying Flamazine® on the wound, pain medication must be given. Paracetamol, Oxynorm and Oxycontin will be used as standard pain medication. The usage and doses of pain medication will be monitored. The burn wound will be cleaned and rinsed with Prontosan® followed by carefully dabbing and drying of the wound. A sufficiently thick layer (at least 2–3 mm) of Flamazine® will be applied directly on the wound. The cream will be covered with a non-adhesive dressing. A net bandage/dressing will be used to keep the dressing in place. This procedure is repeated once every 24 hours until the sixth day post burn. Thereafter, the treatment of all patients in this study arm will consist of Furacine Soluble Dressing (Furacine 2 mg/g ointment) on the seventh day post urn, and Flamazine® on the eighth day post burn. Treatment with Furacine Soluble Dressing and Flamazine® will be alternated until complete wound healing/operation because of the cytotoxicity of the silver particles in Flamazine® on the wound bed when used continuously. In case of wound colonization or infection the treatment will be replaced with another relevant treatment based on the results of the wound culture

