#### Secondary outcomes/study parameters

o*Clinical outcomes:*Need for operation which is evaluated between 10 and 14 days post burn. Reasons for operation are that the experienced burn specialist expects no further wound healing in the next 7 to 11 days of the partial thickness area or a full thickness burn. If the decision to graft is made before 10 to 14 days post burn then the operation will still performed before 10^th^ day post burn day. The only indication for operation before the 10^th^ PBD is when a partial thickness burn becomes a full partial thickness burn. The treatment of full thickness burns is split skin graft in an early stagePercentage TBSA of the study area that covered with skin graftColonization: twice a week a wound swab will be taken from the study area. The wound swab will then be sent for laboratory investigation. In brief, the analysis of the wound swab will include the following steps. The microscopic examination will entail gram-staining. Thereafter, a quantity of the specimen will be cultured to obtain a pure single specimen culture. Finally, the sensitivity of the organisms to specific local therapy will be determined. In case of wound colonization the treatment will be changed to another relevant treatment based on the results of the wound cultureInfection: infection is suspected if a combination of skin redness, pain, swelling, tenderness, warmth, fever or pus draining from the wound is present. Infection is a clinical evaluation of the wound, in presence of absence of positive wound culture, and is judged by a physician at the burn center during each dressing changeNumber of dressing changesUse of systemic antibioticso*Patient-reported outcomes:*Pain will be measured during the application and removal of the wound dressing (procedural pain, measured directly after dressing change) and background pain (measured in the morning and evening). Pain will be measured twice daily during hospital admission by use of a Visual Analogue Thermometer (VAT), which is a numeric scale from 0 (no pain) to 10 (worst imaginable pain)Itching will be measured daily in the evening during hospital admission by use of a VAT [31]Anxiety: the Burn Specific Pain Anxiety Scale (BSPAS) will be scored on day 7 ± 2 post burn and on the day of discharge. The BSPAS is a valid and reliable nine-item self-report scale for the assessment of pain-related and anticipatory anxiety in burned patients [32, 33]Health-related quality of life (HRQoL) will be measured using the following questionnaires, in the week before discharge and at 3, 6 and 12 months post burn:Burn-specific quality of life (QoL) will be measured using the Dutch version of the Burn Specific Health Scale (BSHS)–Brief [34, 35]. The BSHS-Brief is a valid and reliable self-administered questionnaire that covers nine domains (heat sensitivity, affect, hand function, treatment regimens, work, sexuality, interpersonal relationships, simple abilities, and body image). The questionnaire takes 10–15 minutes to complete and 5 minutes to score. Responses are scored by the patient on a five-point scale from 0 (extreme) to 4 (none/not at all) for each of the 40 items. Mean scores are calculated for each of the domainsGeneral HRQoL will be measured using the EuroQol-5D (EQ-5D) questionnaire [36]. This simple and generic description of health status is widely used in studies on clinical and economic appraisal. The EQ-5D outcomes will be converted in utility scores between 0 (death) and 1 (perfect health) based on empirical valuations [37]. From the area under the utility curve during the 12 months of follow-up quality- adjusted life years (QALYs) will be calculatedo*Scar formation*: the following aspects of scar formation will be measured after 3, 6 and 12 months post burn:Scarring will be measured using the Patient and Observer Scar Assessment Score (POSAS), a valid and reliable scale that is designed for the evaluation of all types of scars by professionals and patients. It consists of two numeric scales: the Patient Scar Assessment Scale which is completed by the patient and the Observer Scar Assessment Scale which is completed by the medical staff. The variables scored by the patient are pain, itching, color, stiffness, thickness and irregularity [38–40]. The variables scored by the medical staff include vascularization, pigmentation, thickness, relief and pliabilityElasticity will be measured using a Cutometer (Courage & Khazak, Köln, Germany), a validated instrument to measure the vertical deformation of the skin in millimetres when the skin is pulled by means of a controlled vacuum into a circular aperture [41]Scar color and pigmentation will be measured using the DSM II colorimeter (Dermaspectrometer).This is a validated instrument to measure scar color by a narrow-band simple reflectance meter [41]o*Total (medical and non-medical) costs:* total costs in this study represent direct health care costs (inpatient and outpatient medical costs), direct non-healthcare costs and indirect non-health care costs (productivity loss). Personnel time and used materials for wound care and surgical procedures, hospital days for initial stay and re-admittance and outpatient visits during the first year will be measured prospectively as part of the case record form. Health resource use outside the hospital, travel costs and productivity losses will be recorded by questionnaires filled out by the patients at 3, 6 and 12 months post burn. Cost of dressing changes and surgical procedures will be assessed by translating the personnel time and used materials into costs by means of gross salaries and market prices. The costs of hospital stay and outpatient care in burn centers will be calculated by multiplying the number of hospital days respectively outpatient visits with their cost prices [42]. Other healthcare use will be translated into costs by standard prices [43]. Productivity losses will be valued using the friction cost method [44]o*Baseline parameters:* age, gender, skin type, wound etiology, bacterial contamination at admission, location of the wound, type of wound, TBSA% and co-morbidities. In all patients, the burn depth of the study area will be accurately determined on day 2–5 post burn by clinical evaluation and LDI scan using the moorLDI2-Burn Imager™ (Moor Instruments, Axminster, UK) and, based on pre-defined criteria (Table 1), be classified as superficial, intermediate or deep partial thickness injury. The size of each burn wound is then estimated in TBSA. In a LDI the low-intensity laser beam is scanned across a tissue surface in a raster fashion using a moving mirror. There is no direct contact with the tissue being assessed. The wounds are scanned by a trained research physician or nurse, after removal of topical medication (during regular wound treatment). All research physicians and nurses in both burn centers have followed the same training sessions and have the same experience. The scanning will take 1–5 minutes.

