
**Table 1 Tab1:** Clinical assessment and laser Doppler imaging (LDI) results

Classification	Clinical properties						LDI color
	Blisters	Color/Appearance	Pliability	Capillary refill	Pain	Healing time	
Superficial partial thickness burns	Small blister: intact and open	Pink-red, shiny	Supple	<2 sec	++	Within 14 days	Red
Intermediate partial thickness burns	Blisters: intact and open	Pink-red, shiny and dry	Mix of supple and stiff	<2 sec	+	14–21 days	Yellow
Deep partial thickness burns	Blisters: intact and open	Red, shiny and dry	Mix of supple and stiff	>2 sec	+/-	>21 days or even no spontaneous healing	Blue
Full thickness burns	None	White-yellow, red, brown and black	Stiff	>2 sec	-	No spontaneous healing	Blue

A schedule with baseline and outcome measurements during the study is presented in Table 2.

**Table 2 Tab2:** Time schedule for study procedures and assessments

Procedure/Assessment	Admission	Treatment phase	Follow-up (month)		
			3	6	12
Standard screening, baseline procedures	x				
Check eligibility (inclusion criteria)	x				
Provide patient Information	x				
Obtain written informed consent	x	x (confirmation by patients who were initially non-competent)			
Randomization (Flaminal® vs Flamazine®)	x				
Baseline parameters	x				
LDI		x			
Wound colonization	x	x			
Wound healing		At each dressing change			
Need for surgery of partial and/or full thickness burns and % of study area requiring skin graft		10–14 PBD			
Colonization	x	Swabs on Mondays and Thursdays			
Infection	x	Clinical judgment during dressing changes			
Dressing changes	x				
Use of systemic antibiotics	x				
Pain and anxiety					
Visual analogue thermometer (VAT)	x	Daily, before and after dressing change and in the evening			
Itching	x	Daily in the evening on 7^th^ ±2 PBD and day of discharge			
Burn Specific Pain and Anxiety Score (BSPAS)	x				
Health-related quality of life (HRQoL)		In the last week of hospitalization			
Burn Specific Health Scale Brief (BSHS-Brief)		In the last week of hospitalization	x	x	x
EuroQol-5D (EQ-5D)			x	x	x
Scarring					
POSAS			x	x	x
Cutometry			x	x	x
Dermaspectrometry			x	x	x
Costs		Daily	x	x	x

*LDI* laser Doppler imaging, *PBD* post-burn day

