### Statistical analysis

The analysis will be performed according to the intention-to-treat principle. The baseline patient characteristics will be described as mean ± standard deviation for normally distributed continuous variables, as median (range) for skewed continuous variables, and as number (proportion) for categorical variables. Differences in time to complete re-epithelialization will be compared in both treatment groups will be analyzed with Kaplan-Meier curves and log rank test.

If the baseline characteristics seem unbalanced despite randomization, a multivariable Cox regression analysis will be performed to correct for potentially confounding variables to confirm the primary analysis.

The secondary clinical and patient-reported outcomes on specific follow-up moments will be compared between the treatment groups using the two-sided *t* test or Mann-Whitney test for continuous data, and a two-sided Chi-square test or Fisher’s exact test for categorical data. Repeatedly measured study parameters such as pain and quality of life will be also analyzed using a linear mixed model with treatment as fixed effect and patient as random effect. In the analyses, *p* values <0.05 will be considered statistically significant.

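### The mixed model for repeated outcomes names no time term, so for inpatient pain it can confound treatment with post-burn day

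*Protocol article*

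**What the plan says.** All references are to the protocol article.

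- **Model.** Statistical analysis: "Repeatedly measured study parameters such as pain and quality of life will be also analyzed" by a mixed model, "using a linear mixed model with treatment as fixed effect and patient as random effect". No term for day, visit or time is named.
- **Companion tests.** The same paragraph first states: "The secondary clinical and patient-reported outcomes on specific follow-up moments will be compared between the treatment groups", by t test or Mann-Whitney test for continuous data.
- **Flaminal dressings.** Interventions: "Dressing changes will be performed daily during the first 3 days post burn and thereafter every other day". More frequent changes are allowed for suspected infection, leakage or too little gel.
- **Flamazine dressings.** Interventions: "This procedure is repeated once every 24 hours until the sixth day post burn". After that, "Treatment with Furacine Soluble Dressing and Flamazine® will be alternated until complete wound healing/operation", with Furacine on day 7 and Flamazine on day 8. I read this as still one change a day.
- **Pain.** Secondary outcomes: a 0 to 10 scale, used only during the hospital admission. There is "procedural pain, measured directly after dressing change", and background pain in the morning and evening. Table 2 gives the times as "Daily, before and after dressing change and in the evening".
- **Quality of life.** Secondary outcomes: in the last week before discharge, then at 3, 6 and 12 months post burn, in both arms. Scar scores: 3, 6 and 12 months.

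**The concern.** A model with treatment and a patient intercept compares each arm's average over whatever days were observed. That is harmless if both arms are observed on the same days, or if the outcome does not change over time. For inpatient pain neither can be taken for granted.

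Two features of the design separate the observed days. First, the dressing schedule gives Flaminal fewer procedural-pain readings after day 3, so a larger share of its readings comes from the first days. Second, pain readings stop at discharge. The Background section links faster healing to a shorter stay, and the sample size section expects healing in 6 days with Flaminal and 11 with Flamazine. If the trial hypothesis is right, the Flaminal arm may lose its later readings, and this affects background pain as well.

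If pain falls as the burn heals, both features place Flaminal's readings earlier and higher, and the printed model counts that as a treatment effect. Pain at dressing changes is one of the reasons the article gives for the trial, so the comparison matters although it is secondary.

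**Working it through.** The plan gives no figure to reproduce here, so the check has two parts: the measurement days that follow from the schedules, and the difference the printed model would show if there were no treatment effect.

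**1. Days on which procedural pain is scored**

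Assume the first change on day 1, Flamazine daily, and Flaminal on days 1, 2, 3, 5, 7, 9 and so on, with no extra changes.

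| Stay in both arms | Flamazine: readings (mean day) | Flaminal: readings (mean day) | Shift |
|---|---|---|---|
| 6 days | 6 (3.50) | 4 (2.75) | 0.75 |
| 7 days | 7 (4.00) | 5 (3.60) | 0.40 |
| 11 days | 11 (6.00) | 7 (5.43) | 0.57 |
| 14 days | 14 (7.50) | 8 (6.375) | 1.125 |
| 21 days | 21 (11.00) | 12 (10.25) | 0.75 |

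So the schedule alone shifts the mean day by about 0.4 to 1.1 days, and 14 days is at the high end.

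With unequal stay the shift grows:
- 14 v 10 days, procedural: Flaminal days 1, 2, 3, 5, 7, 9 have mean 27/6 = 4.5, so 7.5 − 4.5 = 3.0 days. Background: 7.5 − 5.5 = 2.0 days.
- 11 v 6 days (the expected healing times, used as stays only for illustration), procedural: 6.0 − 2.75 = 3.25 days. Background: 6.0 − 3.5 = 2.5 days.

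**2. Spurious difference when every patient in an arm has the same stay**

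Spurious difference = fall in pain per day × shift in mean day. The fall is assumed to be linear, 0.1 to 0.3 points per day.
- Equal 14-day stay: 0.1 × 1.125 = 0.11 to 0.3 × 1.125 = 0.34 points.
- 14 v 10 days, procedural: 0.1 × 3.0 = 0.30 to 0.3 × 3.0 = 0.90 points. Background: 0.20 to 0.60 points.

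**3. Rejection rate with no true effect**

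Assume a patient SD of 1.2 and residual SD of 1.5 (neither is in the article), with 41 per arm. The variance of a patient mean is 1.2² + 1.5²/k for k readings.
- Equal 14-day stay: 1.44 + 2.25/14 = 1.601 and 1.44 + 2.25/8 = 1.721. SE = √((1.601 + 1.721)/41) = 0.285. At 0.3 points per day, 0.3375/0.285 = 1.19 and rejection is about 22%; at 0.1 it is about 7%. Simulation gave 6% to 21%.
- 14 v 10 days: 1.44 + 2.25/6 = 1.815. SE = √((1.601 + 1.815)/41) = 0.289. Rejection is about 18% at 0.1 and 88% at 0.3. With both SDs at 2, simulation gave 10% to 48%.

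**4. The same with stay varying between patients**

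Simulated mixed-model fits: gamma-distributed stay, both SDs 1.5, 41 per arm, no treatment effect, 100 runs per scenario, so the rates are rough.

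| Scenario | Spurious difference at falls of 0.1 / 0.2 / 0.3 | Rejection |
|---|---|---|
| Procedural, mean stay 11 in both arms | 0.03 / 0.12 / 0.19 | 7 / 6 / 7% |
| Procedural, mean stay 11 v 6 | 0.27 / 0.54 / 0.91 | 15 / 33 / 59% |
| Background, mean stay 11 v 6 | 0.27 / 0.51 / 0.78 | 13 / 29 / 54% |

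With a day term added, the mean spurious difference lay between −0.05 and +0.02 points in every scenario, and rejection was 1% to 10%, compatible with 5% given the number of runs.

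**5. Quality of life and scars**

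At 3, 6 and 12 months the assessment days are the same by design, so the shift is 0. Only the discharge-week quality-of-life score can fall on different post-burn days.

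**The case against.** The strongest reply is that this is one sentence in a condensed article, about a supplementary analysis of secondary outcomes. It does not say that treatment is the only fixed effect, and the coding of time is commonly left to the analysis plan, which is not shown. That lowers the weight of the point. It does not remove it, because the article goes beyond silence: it lists the model's terms, and time is not among them. If the full plan has a time term, the sponsor need only confirm it.

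Second, with equal stay the effect is modest. This stands. With varying stay averaging 11 days the rejection rate was 6% to 7%. Extra Flaminal changes, which the protocol allows, would bring the schedules closer.

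Third, dressing frequency is part of each regimen, so mean pain per dressing change is a defensible summary without adjustment for day. That is fair for procedural pain, but the article does not name it as the target, and it does not deal with readings cut off by discharge.

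Fourth, the conflict over pain times may be slight, since the reading before a change could be the morning background score. That is possible. But the text also says pain is measured twice daily and then lists procedural plus morning and evening scores, so the times still need to be stated once.

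A reader might also infer that the model leaves no time-specific contrast at all. The article does not support this: the tests at specific follow-up moments provide such contrasts.

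**Conclusion.** The point holds for inpatient pain. As printed, the model can mix treatment with post-burn day: for procedural pain through the dressing schedule, and for all inpatient pain through length of stay. With equal stay the spurious difference is about 0.03 to 0.34 points, with rejection of about 6% to 21%; the upper end requires the steepest assumed fall, the smaller SDs and an identical stay for every patient. With stays of 14 v 10 or 11 v 6 days it is about 0.3 to 0.9 points for procedural pain. The rate of fall, the SDs and the stays are assumptions. The direction, against Flaminal, holds only if pain falls over time.

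Three stronger readings are tempting and not supported:
- **That quality of life is biased in the same way.** At 3, 6 and 12 months the arms are assessed at the same times. A visit term there would only add precision and a treatment-by-visit estimate.
- **That the model compares days instead of treatments.** The schedule alone shifts the mean day by only about 0.4 to 1.1 days, and background pain shifts only if stay differs, which the Background section calls unknown.
- **That false positives near 90% are to be expected.** That figure combines the steepest assumed fall with a fixed four-day gap in stay and no variation in stay between patients. With varying stay, an approximate calculation for the same 14 v 10 case gives about 64%.

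**What to change.** Amend the analysis wording before the data are analysed:

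- Model procedural and background pain separately, each with treatment, post-burn day (categorical or spline) and treatment-by-day as fixed effects and patient as random effect. Report the treatment contrast at stated days.
- For quality of life, use treatment, visit and treatment-by-visit.
- Reconcile the pain measurement times in the Secondary outcomes text with Table 2, and state which reading is procedural and which is background, including on days without a dressing change.
- Leave the tests at specific follow-up moments as planned.

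The cost is a few lines of analysis text. No new data are needed beyond the date of each score, and the Trial status section reports that follow-up was still ongoing.

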### Sample size calculation

The study is designed to demonstrate a clinically relevant difference regarding time to complete epithelialization between the treatment arms. Based on a retrospective study of 70 patients with superficial and deep partial thickness burns of the hand, we expect wounds to heal in 11 days on average with Flamazine**®** and in 6 days on average with Flaminal**®** (pooled standard deviation 7.5 days) [28]. With alpha set at 5 %, 41 patients are needed in both intervention arms to detect a difference in wound healing time with 80 % power. To allow for 10 % attrition, a total of 90 patients will be included in the study.

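### Admission pain and itch scores are scheduled but left out of the pain and itch models, so the comparisons are valid but less precise than they could be

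*Protocol article*

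**What the plan says.** In Table 2 of the protocol article, the VAT pain row and the itching row each carry a mark under Admission and a separate daily entry under Treatment phase. The Secondary outcomes section gives the inpatient frequency ("Pain will be measured twice daily during hospital admission"), with background pain scored morning and evening, procedural pain scored directly after the dressing change, and itch scored each evening.

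The Statistical analysis section gives two routes for these outcomes. At specific moments they are compared by "two-sided *t* test or Mann-Whitney test for continuous data". Repeated measures, with pain as a named example, are also analysed by a "linear mixed model with treatment as fixed effect and patient as random effect". The only covariate adjustment in the section is a Cox model for the primary outcome, used if baseline characteristics look unbalanced. Pain and itch are not in the list of baseline parameters.

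**The concern.** Pain and itch are self-reported, and patients are likely to start at different levels. If a patient's starting level predicts later scores, a comparison that ignores it carries avoidable noise. The random patient effect does not remove that noise: treatment varies between patients, so between-patient variation stays in the standard error of the treatment effect unless a covariate explains part of it.

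At stake is the width of the confidence intervals for two secondary outcomes. The trial was sized only "to detect a difference in wound healing time with 80 % power", and no effect size or power is set for pain or itch. The Background section says that the two products have not been compared on pain during dressing changes, so precision on pain is worth keeping.

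**Working it through.** **Inputs.** From the Sample size calculation: 41 patients per arm (82 in all), alpha 5%, power 80%. Sidedness is not stated there; two-sided is assumed, in line with the tests named for secondary outcomes. No SD, effect size or baseline correlation is given for pain or itch, so effects are expressed in SD units and rho is assumed over 0.1 to 0.7.

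**The plan's own figure.** It belongs to healing time: a difference of 11 - 6 = 5 days with SD 7.5. The usual two-means formula gives n = 2 × (7.5 × (1.960 + 0.842) / 5)² = 35.3, so 36 per arm (37 by the t distribution). The stated 41 is larger and would give about 85% power by that formula. It errs on the safe side. Nothing below depends on how it was derived; it serves only as the number per arm.

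**Effect detectable without adjustment.** d = (1.960 + 0.842) × √(2/41) = 2.802 × 0.2209 = 0.619 SD at 80% power.

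**Effect of adjusting for the admission score, one later score as outcome.** Variance ratio = 1 - rho². Power = Φ(2.802 / √(1 - rho²) - 1.960). Equivalent unadjusted sample = 82 / (1 - rho²).

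| rho (assumed) | Variance ratio | Power | Equivalent total N |
|---|---|---|---|
| none used | 1.00 | 80% | 82 |
| 0.1 | 0.99 | 80.4% | 83 |
| 0.3 | 0.91 | 83.6% | 90 |
| 0.4 | 0.84 | 86.4% | 98 |
| 0.5 | 0.75 | 89.9% | 109 |
| 0.7 | 0.51 | 97.5% | 161 |

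For example, at rho 0.5: 2.802 / 0.866 - 1.960 = 1.276, and Φ(1.276) = 0.899.

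**Mean of several later scores, as in the mixed model.** If all scores share one correlation rho, the ratio is 1 - rho² / [(1 + (m - 1)rho)/m]. For m = 7 and rho 0.3: (1 + 1.8)/7 = 0.40, and 1 - 0.09/0.40 = 0.775. For rho 0.5: (1 + 3)/7 = 0.571, and 1 - 0.25/0.571 = 0.56. So averaging over days does not remove the gain. These two ratios are favourable: if the admission score correlates less with later days than those days do with each other, the gain is smaller.

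**The case against.** The strongest objection is that the article does not prove a usable pre-treatment score exists. A reader might infer one from the exclusion of patients already on topical therapy and from the statement that treatment "will be initiated within 24 hours after admission". The documents do not carry that inference all the way:

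- The 24-hour limit is an upper bound and is stated only for Flaminal Forte.
- Randomization stands in the same Admission column, and the order of scoring, randomization and first application is not given.
- Itch is an evening score, so the first one may follow the first application.
- Procedural pain is scored after a dressing change and may have no pre-treatment counterpart.
- The BSPAS has its mark under Admission, although the Secondary outcomes section places it around day 7 and at discharge.
- Dressing changes and antibiotic use are marked under Admission only, which suggests that the column is used loosely.

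These doubts stand, and they limit the scope to background pain and itch scores whose recorded time is before first application. They do not remove the point. Pain and itch have an admission mark in addition to a treatment-phase entry. Colonization shows the same pattern, and bacterial contamination at admission is a listed baseline parameter.

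It can also be said that an article condenses the plan and that covariates are often left to the analysis plan. That has weight, and the article does not say that no other term may enter. But it names the fixed and random terms and says where adjustment will be used, so the point concerns a stated choice.

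Two other readings go too far. One is that the unadjusted comparison is biased or invalid; randomization protects it. The other is that admission scores enter the model as outcomes and dilute the effect. The article does not say so, and the dilution would be small: with one such score among about 20 (two a day over an assumed 10-day stay), about 1/20 = 5%.

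**Conclusion.** The point holds as a minor efficiency issue on secondary outcomes. The planned comparisons of pain and itch are valid, and the primary analysis is untouched. They forgo a gain that depends wholly on an unstated correlation: negligible at rho 0.1, about 4 percentage points of power at rho 0.3 and about 10 at rho 0.5, for a 0.62 SD effect at 41 per arm. All rho values are assumptions, and the 0.62 SD is a reference effect, not one that the protocol sets for pain or itch. The conclusion also assumes that enough patients have a score recorded before first application; the trial records must confirm this.

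**What to change.** In the Statistical analysis section, add the admission score of the same scale as a fixed covariate in the background-pain and itch models. For a comparison at a single moment, the same covariate can enter a linear model (ANCOVA). Use as covariate only a score already recorded before the first application of the allocated product, and use only later scores as outcomes. Keep patients without such a score, for example those sedated at first, in the analysis by mean imputation or a missing indicator, with the same rule in both arms. Leave the BSPAS out, since its admission mark conflicts with the text, and claim no matching baseline for procedural pain.

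The cost is one extra parameter, a rule for missing starting scores and a few lines of text. The Trial status section reports recruitment complete on 20 October 2015, so the timing rule can only select among scores already recorded; if few qualify, the gain shrinks accordingly. Because the trial is open, the change should be dated and made before outcomes are compared by arm.
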